#### Blinding

In study arm 1 the result of the CYP test is openly revealed to psychiatrists in charge of treatment, while both patients and psychiatrists in study arm 2 and 3 are blinded to the CYP test result. Study personnel involved in the rating of patients at baseline and follow up will be blinded to the patients' study arm allocation and CYP test result. Study personnel performing statistical analyses will be blinded to the study arm allocation.

#### Intervention and treatment

In study arm 1 the genotype information is given to the physician in charge of treatment and can be used to direct the psychopharmacological treatment in accordance with the current guidelines from Sct. Hans hospital (Appendix 2 a and 2 b). In the guidelines, the genotype is translated to the clinical designation "normal", "slow" or "fast" metabolizer of CYP2D6 or "normal" or "slow" metabolizer of CYP2C19. Different treatment options for the different genotypes are described in the clinical guidelines.

In study arm 2 the genotype information is not revealed. The intervention consists of an intensified clinical monitoring of treatment effect, side effects and patient perspective. Staff personnel is trained in the use of a clinical manual that builds on a selection of validated questions from the Scale for the Assessment of Positive Symptoms (SAPS (17)), Side effect score (Udvalg af Kliniske Undersøgelser (UKU (18) and Rating of Medical Influences (ROMI (19)) (Appendix 3). The manual has to be used at least once in a quarter (every third month), which is monitored by the study personnel. Data registered by the patients' primary contact person are not used as outcome measures in the study but only as intervention tool for the optimization of the medical antipsychotic treatment.

In study arm 3, (Control arm) treatment followed usual local practice. The genotype information is not revealed.

To support medical decisions in all study arms the physician in charge of treatment and the primary contact person is allowed to contact the Drug Information Service at the Clinical Pharmacological Unit at Bispebjerg University Hospital, weekdays between 9 and 14 to obtain information on antipsychotics CYP2C19 / CYP2D6 dependency, need for dose adjustment and interpretation of drug concentration measurements, etc. Still, the final treatment decision is made by the physician in charge of treatment.

#### **Data recording**

Immediately after the inclusion, the following information is recorded:

- Demographic data (age, gender, weight and height)
- History of the disease
- Symptom score (SAPS score)
- Side effect score (Udvalg af kliniske undersøgelser (UKU) score)
- Medical history (current and historical)
- Compliance (ROMI)

The following information is registered 12 months after study conclusion:

- Symptom score (SAPS score)
- Side effect score (Udvalg af klinisk undersøgelser (UKU) score)
- Compliance (ROMI)
- Weight

- Metabolic functions (plasma cholesterol, fasting blood glucose, plasma triglyceride, plasma prolactin (only when available in PEM))

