## **Design**

A prospective blinded randomized trial designed as parallel study with three study arms; two intervention arms and one control arm. The study duration is 12 months. Outcome measures are recorded at baseline and 12 months follow up.

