## **Secondary effect parameters:**

- a. Compliance. (Participants are categorized as fully, partially or non-compliant based primarily on the patient's own report in a non-judgmental interview. In addition to that, information from serum concentration measurements are collected and patient's understanding of the importance of medical treatment is rated using Rating of Medication Influences (ROMI) scale (18).
- b. Number of drug changes / dose changes
- c. Positive symptoms in schizophrenia (Scale of Assessment of Positive Symptoms (SAPS)) score (17).
- d. Side effect score (Udvalg af Kliniske Undersøgelser (UKU) score) (18), weight, metabolic functions (plasma cholesterol, solid blood sugar, plasma triglyceride, plasma prolactin (only when recorded routinely in the patient's Personal Electronic patient Profile (PEM))
- e. Number and length of admissions during the study period

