#### Recruitment, randomization

Study participants are recruited among patients who are affiliated with the outpatient clinics in the Capital Region. After informed consent, patients are genotyped for CYP2D6 and 2C19. Following primary stratification according to the genotype and use of antipsychotic depot preparations, patients are randomized to one out of three study arms or exclusion from the study. Inclusion continues until there are 20 extreme metabolizers are included in each study arm. Based on an expected frequency of 10% poor metabolizers, a total of 600 patients needs to be screened, of which 100 (20 extreme and 80 normal metabolizers) are included in each study arm and 300 are randomly excluded.

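### Data recording dates the follow-up ratings 12 months after the study concludes, whereas Design puts them at 12 months; the two sections must be reconciled

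*Protocol*

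**What the plan says.** The Protocol's Design section fixes the time frame: "The study duration is 12 months" and "Outcome measures are recorded at baseline and 12 months follow up".

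The Data recording section holds the item lists. The baseline list opens with "Immediately after the inclusion, the following information is recorded". The follow-up list opens with "The following information is registered 12 months after study conclusion" and names the SAPS score, the UKU score, ROMI, weight and the metabolic measures.

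Two other places bear on timing:

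- Secondary effect parameters counts admissions over the study itself: "Number and length of admissions during the study period".
- Recruitment, randomization makes entry staggered: "Inclusion continues until there are 20 extreme metabolizers are included in each study arm".

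**The concern.** Design and Data recording give different times for the same ratings. Design states a time point without listing items. Data recording lists the items and gives a different time point. Someone preparing a visit schedule from the item list would be led to the later date.

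The items concerned feed three of the five secondary outcomes: compliance (a), positive symptoms (c), and side effects with weight and metabolic functions (d). If the later date were used, these would describe patients after the 12-month study, while admissions (e) would describe them during it. The secondary outcomes would then not share a window. Under one reading of the sentence, the length of follow-up would also differ between patients. Neither consequence can be undone once the ratings have been made.

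**Working it through.** No power or sample-size formula bears on this point. The check compares the sections and adds months.

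**Inputs**

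- Study duration: 12 months (Design).
- Follow-up time according to Design: 12 months. I count this from inclusion, because the baseline data are taken at inclusion (Data recording).
- Follow-up time according to Data recording: 12 months after the study concludes.
- Entry: staggered until each arm has its 20 extreme metabolizers (Recruitment, randomization). The length of the recruitment period, R months, is not given.

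**Step 1. Design's own figure.** The rating falls at month 12 and the study period ends at month 12. The gap is 12 − 12 = 0 months. The 12-month duration has to be per patient: with staggered entry, a trial lasting 12 calendar months in all could not give every patient a 12-month follow-up.

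**Step 2. Data recording, with conclusion read as the end of the patient's own study period.** Time of rating = duration + 12 = 12 + 12 = month 24. The gap after the study period is 24 − 12 = 12 months, the same for every patient.

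**Step 3. Data recording, with conclusion read as the end of the whole trial.** Assume that the trial ends when the last patient included completes 12 months. The last patient is then rated at 12 + 12 = month 24 and the first at R + 12 + 12 = month 24 + R. Follow-up varies across patients by R months. As R is not given, the documents support only the statement that ratings fall at month 24 or later and at varying times.

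**Step 4. Is there a reading that agrees with Design?** Only if the anchor is inclusion: 0 + 12 = month 12, which matches Step 1. No other section describes a post-study year or defines the study's conclusion differently. The Blinding section knows only two rating occasions, baseline and follow-up.

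**Step 5. What is affected.**

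| Outcome | In the follow-up list? |
|---|---|
| Primary a, b (time to discontinuation, persistence) | No |
| Secondary a (compliance) | Yes, through ROMI |
| Secondary b (drug and dose changes) | No |
| Secondary c (SAPS) | Yes |
| Secondary d (UKU, weight, metabolic measures) | Yes |
| Secondary e (admissions) | No; counted over the study period |

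**The case against.** The strongest reply is that this is a slip of wording or translation and that no one intended a rating at month 24. Design is unambiguous. The baseline sentence in Data recording is anchored to inclusion, and no section plans for a further year. The text is loose elsewhere too: the blood sugar measure is called solid in Secondary effect parameters and fasting in Data recording. I accept this as the likely explanation. It makes the remedy easy but does not remove the conflict, because the faulty sentence is an operative instruction and staff should not have to guess its meaning.

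The second reply is that the reach is limited. That stands: the primary outcomes are not in the list, and the sample size rests on time to discontinuation.

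A reader might also infer more than the text supports:

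- **That the interventions will have ended and arms 2 and 3 will be unblinded by the time of the rating.** The documents do not say so. The arm 2 rule, "The manual has to be used at least once in a quarter (every third month), which is monitored by the study personnel", carries no end date. Blinding to the CYP result has none either, and the raters are blinded at follow-up whenever it takes place. A lapse at month 12 would be an inference from the study duration alone. In arm 1, a genotype once revealed stays known.
- **That late ratings would pull the arm comparisons toward no difference.** This depends on the lapse just described and on effects fading, neither of which the protocol establishes.
- **That follow-up would reach some particular number of years.** This needs a value for R, which is not given, together with the trial-end reading.

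**Conclusion.** The point holds as an internal contradiction in a measurement rule. Taken literally, Data recording moves SAPS, UKU, ROMI, weight and the metabolic measures from month 12 to month 24 per patient, or to month 24 and later at varying times if the end of the whole trial is meant. Both lie outside the 12-month study period in which admissions are counted.

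This rests on two readings of the text: that Design's 12 months run from inclusion, and that the study period named for admissions is the 12 months given in Design. The trial-end variant further assumes that the trial closes when the last patient completes follow-up.

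The conclusion concerns the text. It does not show that ratings will in fact be taken late, and it supports no statement on the direction of bias, on blinding or on how long the arm 2 manual is used. The sentence is more than clerical because it governs when three of the five secondary outcomes are measured, and it should be corrected before anyone schedules visits from it.

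**What to change.** Reconcile Data recording with Design by changing the opening sentence of the follow-up list to: *The following information is registered 12 months after the patient's inclusion (randomization).* If inclusion and randomization can fall on different days, name the one that starts the clock. A visit window may be added, but the conflict is resolved without it.

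The cost is one sentence. No visit is added, because Design already plans the 12-month rating, and neither sample size nor power changes. If a later rating was in fact intended, Design would have to say so instead. This correction does not require the protocol to set or alter the length of the arm 2 intervention.

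### The recording schedule gives the four metabolic laboratory outcomes no baseline value, and prolactin depends on routine testing that may differ by arm

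*Protocol*

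**What the plan says.** The protocol's Design section sets a general rule: "Outcome measures are recorded at baseline and 12 months follow up". Under Secondary effect parameters, item (d) includes "metabolic functions (plasma cholesterol, solid blood sugar, plasma triglyceride, plasma prolactin (only when recorded routinely", so these laboratory values are outcomes. The qualifier there reads in full "only when recorded routinely in the patient's Personal Electronic patient Profile (PEM".

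Data recording then gives two lists. The first opens with "Immediately after the inclusion, the following information is recorded" and covers demographics, disease history, SAPS, UKU, medical history and ROMI. It has no cholesterol, glucose, triglyceride or prolactin. The second list, for follow-up, adds "Metabolic functions (plasma cholesterol, fasting blood glucose, plasma triglyceride, plasma prolactin (only when available in PEM".

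Handling of biological material describes the metabolic bloods as ordinary clinical tests that accompany antipsychotic treatment. No draw ordered by the study is stated for any arm. Under Intervention and treatment, arm 2 receives "intensified clinical monitoring of treatment effect, side effects and patient perspective", with the manual used at least every third month. Arm 3 receives usual local care.

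**The concern.** There are two separate issues.

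The first is the schedule. The general rule asks for every outcome at both times, but the baseline list leaves out four of them. If staff follow the list, the analyst has no baseline value to adjust for. An analysis plan cannot repair this later, because it cannot supply data that were never collected.

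The second is how follow-up values arise. Prolactin is used only if the clinic happened to measure it. Arm 2 adds regular structured questioning about side effects. The protocol's Background says that usual recording of adverse reactions is uneven, with sexual side effects recorded in only 23% of cases. The interviews may therefore bring out complaints that usual care would miss, and those complaints may lead to a blood test. The patients with a value could then be selected differently in arm 2 than in the control arm, and randomization would no longer protect the comparison of tested patients.

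**Working it through.** The protocol gives no figure on this point, so there is none to reproduce. The check sets the sections side by side and then sizes each issue on stated assumptions.

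**1. The schedule**

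| Measure | Outcome? | Baseline list | Follow-up list |
|---|---|---|---|
| SAPS, UKU, ROMI | yes | yes | yes |
| Weight | yes, in (d) | yes, "Demographic data (age, gender, weight and height" | yes |
| Cholesterol, glucose, triglyceride | yes, in (d) | no | yes |
| Prolactin | yes, in (d) | no | yes, if in the electronic record |

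Only the laboratory values break the general rule. The nearest baseline entry is "Medical history (current and historical", which names no laboratory value.

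**2. Cost of having no baseline value**

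Let rho be the correlation between baseline and follow-up, with equal variances and a roughly linear relation. The documents give no rho, so 0.3, 0.5 and 0.7 are assumed. Variance of the arm difference, relative to follow-up only (= 1):

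- adjusted for baseline (ANCOVA): 1 − rho²
- change from baseline: 2(1 − rho)

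| rho | ANCOVA | Change score | Patients needed, follow-up only ÷ ANCOVA |
|---|---|---|---|
| 0.3 | 0.91 | 1.40 | 1/0.91 = 1.10 |
| 0.5 | 0.75 | 1.00 | 1/0.75 = 1.33 |
| 0.7 | 0.51 | 0.60 | 1/0.51 = 1.96 |

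The ratios assume a baseline value for every patient, and the gain shrinks as fewer have one. A change score is less precise than follow-up only when rho is below 0.5.

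**3. Possible bias from selective testing**

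Let Y be the follow-up value and π(Y) the probability of being tested. The mean among tested patients is E[Y·π(Y)] / E[π(Y)]. If π does not depend on Y, this is the true mean in each arm, whatever the testing rates. If π is the same function in both arms, or one arm's is a constant multiple of the other's, the arm difference is unbiased. Bias therefore needs testing that depends on the value, in a way that differs by arm.

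Illustration with no true effect, Y standard normal, 100 patients per arm (from Recruitment, randomization) and an assumed logit π = a + bY. Type I error is a normal approximation with SD 1.

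| Control (a, b) | Arm 2 (a, b) | Tested, control / arm 2 | Arm 2 − control (SD) | Type I error |
|---|---|---|---|---|
| −1, 0 | 0, 0 | 27% / 50% | 0.00 | 5% |
| −1, 0.5 | −1, 0.5 | 28% / 28% | 0.00 | 5% |
| −1, 0.5 | 0, 0.5 | 28% / 50% | −0.11 | 7% |
| −1, 0.5 | −0.5, 1 | 28% / 40% | +0.16 | 10% |
| −1, 1 | 0, 1 | 30% / 50% | −0.17 | 12% |
| −1, 1 | 0, 0 | 30% / 50% | −0.59 | 72% |

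The sign changes with the assumptions. The last row is an extreme case in which control testing depends strongly on the value and arm 2 testing does not depend on it at all.

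Numbers would also be small in the planned subgroup comparisons. With 20 extreme metabolizers per arm, testing rates of 28% and 50% leave 20 × 0.28 = 5.6 and 20 × 0.50 = 10 values.

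**The case against.** The case on the other side is substantial.

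- **Baseline values may exist.** The Design rule asks for them, and because these are routine tests, earlier results may be in the record. A reader might infer that change on treatment can never be studied. The documents do not support that. They show only that no baseline value is scheduled.
- **A missing baseline is not a bias.** Randomization balances earlier treatment in expectation, so follow-up values can be compared fairly. This stands.
- **The link from interview to blood test is an inference.** A reader might conclude that arm 2's interviews do change who is tested. No section says so. For cholesterol, glucose and triglyceride, the description of routine follow-up for treated patients weakens the idea further. Arm 1 may also differ from control, since Appendix 1 lists closer observation and regular serum concentrations for some genotypes.
- **A single striking example proves little.** Suppose 20% truly have raised prolactin in both arms. Control tests 60% of them and 20% of the rest: 0.12/0.28 = 43% raised among those tested. Arm 2 tests 80% and 50%: 0.16/0.56 = 29%. The gap of 14 points is correct arithmetic, but every input is assumed. With 28 and 56 tested, its standard error is √(0.429·0.571/28 + 0.286·0.714/56) = 0.111, so z = 1.28 and p is about 0.20. It cannot serve as an estimate of the bias.
- **Windows and missing data often belong in the SAP**, which is not shown. This is fair for the analysis rules, but not for the baseline list, which decides what is collected.

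The contradiction in the schedule and the reliance on opportunistic prolactin values survive these objections.

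**Conclusion.** The point holds as a contradiction in the recording schedule, with a separate and conditional risk in how values are obtained.

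The contradiction is certain on the text: four outcomes are missing from the baseline list although Design requires outcomes at baseline. Its price is precision, a factor of about 1.1 to 2.0 in patients needed, given the assumed correlations and complete baseline data.

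The risk of selection is plausible but not shown. It is clearest for prolactin, where the bracket certainly applies. Whether the bracket covers all four analytes is ambiguous. In the scenarios where testing depends on the value and differs by arm, the spurious difference was −0.17 to +0.16 SD, and −0.59 SD in the extreme case. It was zero where testing did not depend on the value or did so identically in both arms. The documents do not say which situation applies.

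Only laboratory components of one secondary parameter are affected. Weight, in the same parameter, has a baseline value, and no primary outcome is touched.

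**What to change.** In Data recording, add cholesterol, glucose, triglyceride and prolactin to the baseline list, taken from existing electronic or laboratory records within a stated period before randomization. This brings the list into line with Design.

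At follow-up, take the value nearest month 12 in one window that is the same for all arms. Count the window from inclusion, because the introduction to the follow-up list currently counts its 12 months from the end of the study. State whether the electronic-record qualifier applies to prolactin alone or to all four analytes.

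Compare arms on the follow-up value adjusted for baseline. Keep patients who have a follow-up value but no baseline, for example with a missing-baseline indicator. Restricting to patients with both values would require two opportunistic tests and so tighten the selection.

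Report the number tested per arm for all four analytes. Present prolactin descriptively, with no between-arm test. Baseline adjustment does not cure selective testing, so the counts are what let a reader judge it.

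The cost is some record extraction, with no new blood sample, and the loss of any between-arm claim for prolactin.

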### **Handling of biological material**

Blood samples for the analysis of metabolic functions and serum concentration measurement of antipsychotics are routine tests and part of the clinical follow-up of patients receiving antipsychotics. Blood samples are analyzed by the Clinical Biochemical Department at Bispebjerg Hospital or the laboratories the hospital usually collaborates with. Blood samples are destroyed after analysis.

Blood samples for genotype analysis are sent to the Research Institute at Sct. Hans Hospital in Roskilde. The blood samples will after data anonymization be included in the Research Institute's biobank.

### **Data processing**

Data comparisons are made both between the two study arms, but also between the subgroups of extreme and normal metabolizers in each study arm. Due to the unpaired and presumably nonparametric character of our data, we plan to use Mann-Whitney's rank sum test, chi squared test and log rank test hypothesis testing. For continuous data, ANOVA is used. The level of significance is 5%. Since the selected power measurements are interdependent, it is not necessary to correct for the risk of mass significance.

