## **Purpose**

- To investigate whether CYP test guided treatment improves antipsychotic drug treatment in patients with schizophrenia compared to clinical dose titration.
- To investigate whether intensified clinical monitoring focusing on tolerability, effectiveness and patient's perception of medical treatment can improve antipsychotic drug treatment in patients with schizophrenia compared to control.
- To compare the effect of CYP test guided treatment and intensified clinical monitoring on antipsychotic drug treatment in patients with schizophrenia.

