## **Study Population**

300 patients diagnosed within the schizophrenic spectrum, defined as disorders within the F2 spectrum of ICD-10 (16); 60 extreme metabolizers (PM or UM for CYP2D6 or CYP2C19) and 240 normal metabolizers (EM or intermediate metabolizers (IM) for CYP2D6 or CYP2C19).

The sample size calculation is based on the need to make statistically sound comparisons between the smallest subgroup of the study population, i.e. extreme metabolizers. The calculation is based on the primary outcome "time to discontinuation of initial antipsychotic treatment". Based on the literature, we estimated the smallest relevant difference (d0) to be 45 days and the standard deviation of this parameter to be 39.3. With a type-1 error of 5% and a type 2 error of 10%, n is calculated from the formula:  $n_1 = n_2 = n_3 = 2 \cdot (t_{2\alpha} + t_{2\beta})^2 \cdot \frac{\sigma^2}{d_0^2}$

SD / d0^2 = 19.5, i.e. 20 extreme metabolizers in each study arm. Assuming a prevalence of 10%, approximately 600 patients must be screened to identify 60 extreme metabolizers.

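### Data processing lists comparisons that do not match the three-arm design: it refers to two arms, and its only subgroup contrast is by genotype within an arm, not the between-arm contrast among extreme metabolizers that sets the sample size

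*Protocol*

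**What the plan says.** Under Data processing, the protocol fixes the comparisons in one sentence: "Data comparisons are made both between the two study arms, but also between the subgroups of extreme and normal metabolizers in each study arm". The section then names Mann-Whitney, chi-squared and log rank tests, with ANOVA for continuous data, a 5% significance level and no multiplicity correction.

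Other sections describe a different structure:

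- Design: the trial is "designed as parallel study with three study arms; two intervention arms and one control arm".
- Purpose asks three questions: "To investigate whether CYP test guided treatment improves antipsychotic drug treatment in patients with schizophrenia compared to clinical dose titration"; whether intensified monitoring "can improve antipsychotic drug treatment in patients with schizophrenia compared to control"; and "To compare the effect of CYP test guided treatment and intensified clinical monitoring on antipsychotic drug treatment in patients with schizophrenia".
- Study Population bases the sample size on the "need to make statistically sound comparisons between the smallest subgroup of the study population, i.e. extreme metabolizers", using a formula with three equal groups and 20 extreme metabolizers per arm.
- Recruitment, randomization stratifies by genotype (and depot use) and continues until each arm holds 20 extreme metabolizers, alongside 80 normal metabolizers.

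**The concern.** Two things in the Data processing sentence do not fit the rest of the protocol.

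First, it refers to two arms without saying which. Three arms give three pairs, and Purpose asks about all three. Read literally, at most one of the three questions has a named analysis.

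Second, the subgroup comparison it states is between genotypes inside an arm. Genotype is a stratification factor and is not assigned at random. A difference between extreme and normal metabolizers in one arm therefore estimates an association with genotype, whatever the intervention does, and answers none of the three questions in Purpose. Background already links poor metabolizers to more adverse reactions and ultra-rapid metabolizers to treatment failure, although it gives no figure for time to discontinuation.

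The comparison that determines 20 per arm, 60 extreme metabolizers and 600 screened patients is between arms, within the extreme metabolizers. An analyst who follows Data processing to the letter would not run it. Someone could also be tempted to read a significant genotype gap in one arm and a non-significant one in another as evidence about the intervention.

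**Working it through.** **Inputs.** From Study Population: smallest relevant difference d0 = 45 days, SD = 39.3, type 1 error 5%, type 2 error 10%, 20 extreme metabolizers per arm. From Recruitment, randomization: 20 extreme and 80 normal per arm, so 100 per arm. The powers below use a two-sided 5% test and the normal approximation on days, as the protocol's formula does. They ignore censoring at 12 months.

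**1. Which contrast does the stated sample size fit?** The formula is n = 2·(sum of quantiles)²·SD²/d0², with SD²/d0² = 1544.49/2025 = 0.7627.

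- Normal quantiles 1.960 + 1.282: n = 16.03, so 17.
- Exact t: 18 per group (power 0.916).
- Type 2 error also treated as two-sided, 1.960 + 1.645: n = 19.82, so 20.

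The printed 19.5 is not hit exactly, but the stated 20 per arm is reproduced by the third variant and is within two of the exact-t answer. Each variant compares two equal groups. That fits 20 v 20 extreme metabolizers between arms. It does not fit 20 v 80 within an arm or 100 v 100 over all patients.

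**2. The three contrasts side by side.** SE = 39.3·√(1/a + 1/b); power = Φ(45/SE − 1.96).

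| Contrast | Sizes | SE (days) | Power for 45 days | Randomized? | Listed in Data processing? |
|---|---|---|---|---|---|
| Arms, among extreme metabolizers | 20 v 20 | 12.43 | 95.2% (exact t 94.2%) | yes | no |
| Extreme v normal, within an arm | 20 v 80 | 9.83 | 99.6% | no | yes |
| Whole arms | 100 v 100 | 5.56 | >99.9% | yes | yes, for two unnamed arms |

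**3. What is lost if only whole arms are compared?** The last row supposes 45 days in every patient. Appendix 1 gives normal metabolizers standard doses, so a benefit of testing might be confined to extreme metabolizers. This is an assumption; the protocol does not state it. Then 45 days in 20 of 100 patients is 0.20 × 45 = 9 days overall.

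- SD 39.3 in both arms: 9/5.56 = 1.62, power Φ(1.62 − 1.96) = 37%.
- Allowing for the extra spread in the tested arm, variance 1544.49 + 0.2·0.8·45² = 1868.49: SE = √((1868.49 + 1544.49)/100) = 5.84, power 34%.

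**4. How often could within-arm tests mislead?** Suppose the genotype gap is the same in two arms, so the intervention does not alter it. If each within-arm test has power p, the two disagree on significance with probability 2p(1 − p).

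- Gap 1.96 × 9.83 = 19 days: p = 0.50, disagreement 50%.
- Gap (1.96 + 0.84) × 9.83 = 28 days: p = 0.80, disagreement 32%.
- Gap 45 days: p = 0.996, disagreement below 1%.

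The protocol gives no genotype gap, so these are illustrations. The rate runs from near 0 to 50%.

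**5. The arm-by-genotype interaction.** SE = 39.3·√(2/20 + 2/80) = 13.89 days. If the arm effect differs between genotypes by the full 45 days, power is Φ(45/13.89 − 1.96) = 90%. If it differs by half that, 22.5 days, power is Φ(1.62 − 1.96) = 37%.

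**The case against.** The strongest reply is that the rest of the protocol leaves little doubt about what was meant. Purpose, Design, the sample size formula, Recruitment, Blinding and Intervention all fix three arms, so the count in Data processing looks like a slip. ANOVA, listed there, can take three groups. Study Population says outright that comparisons among extreme metabolizers drive the sample size, and the subgroup wording could loosely mean arms compared within each genotype group. The questions in Purpose concern patients with schizophrenia, so a randomized whole-arm comparison addresses them once the arm count is corrected.

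Most of this stands, and it rules out three stronger readings that a reader might infer:

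- **That the arm comparison among extreme metabolizers was never planned.** Study Population shows that it was intended. Data processing fails to list it.
- **That the trial cannot say whether testing helps.** The whole-arm comparison is randomized and bears on the stated purposes. Only the question about extreme metabolizers depends on the missing contrast.
- **That the protocol commits the error of comparing within-arm p-values, with a known error rate.** It nowhere says that within-arm tests are evidence on the intervention, and the 50% and 32% rates rest on genotype gaps it does not give.

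The reply does not remove the inconsistency. The comparisons are stated in the protocol and stated in a form that conflicts with its design and sizing, so this is not detail left for a statistical analysis plan.

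**Conclusion.** The point holds as an inconsistency between Data processing and the Purpose, Design, Study Population and Recruitment sections. The arm count is wrong for this trial, the stated subgroup contrast is not randomized, and the contrast behind 20 per arm is not among the listed comparisons.

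If the sentence is followed literally and any benefit is confined to extreme metabolizers, power falls from about 95% for the sized contrast to about 34 to 37% for whole arms. This rests on the protocol's 45 days and SD 39.3, uncensored days and that assumed confinement. If the benefit is 45 days in everyone, the whole-arm comparison loses nothing. The wording should be settled before analysis because it concerns the comparison that justified the sample size.

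**What to change.** In Data processing, replace the sentence on comparisons with a statement that:

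- arm 1 v 3, arm 2 v 3 and arm 1 v 2 are each compared in all randomized patients and, as the sized comparison, among extreme metabolizers, using the tests already named (log rank for time to discontinuation);
- extreme v normal comparisons within an arm are descriptive and are not evidence on the intervention;
- any claim that the effect differs by genotype rests on an arm-by-genotype interaction and not on within-arm p-values set side by side, with a note that the sample size was not derived for that test. The choice of model can be left open.

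The cost is a few sentences. No new data are needed and the sample size does not change. Even if the 5% were divided over the three pairwise contrasts, which this fix does not require, 20 v 20 would keep Φ(45/12.43 − 2.39) = 89% power on the protocol's inputs.
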